#### Perceived improvement

The item “Have your hot flushes improved in the last 4 weeks?” (yes/no) is used as a stratum for the second randomization and as an indicator (“yes” as a requirement) for the qualitative interview.

### Data management

All data collection procedures have been made semi-manual. To reduce errors in data entry, every item answer is labeled with the original questionnaire score. After data entry, 10% of the data is controlled. If the number of mistakes exceeds 5% per case, another 10% of the data is controlled, etc. Plausibility checks are conducted before the statistical analyses.

### Statistical analyses

All hypotheses are tested two-sided with an *α*-level of 0.05.

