**Methods/design:**

In this assessor-blinded, randomized-controlled trial, *n* = 100 women experiencing five or more daily hot flushes of at least moderate severity and bothersomeness are assigned 1:1 to a 4-week OLP treatment or no treatment. To explore the duration and maintenance of placebo effects, the OLP group is randomized a second time to either discontinue or continue the OLP treatment for another 4 weeks. All participants receive a briefing about placebo effects and study visits at baseline, post-treatment (4 weeks), and follow-up (8 weeks, OLP group only). Qualitative interviews about subjective experiences with the OLP treatment are conducted.

Primary outcomes are differences between the OLP and the no-treatment group in the hot flush composite score (frequency × severity), and bothersomeness of hot flushes as assessed with the Hot Flush Rating Scale at post-treatment. Secondary outcomes include hot flush frequency, health-related quality of life, global improvement, and the number of responders at post-treatment. Data are analyzed by fitting (generalized) linear mixed models. An exploratory analysis of maintenance and duration is performed including follow-up data.

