### Power analysis

The power calculation is based on our primary outcome hot flush score. The software G*Power was used to calculate the sample size a priori [42]. Since no OLP study has been conducted in the field of hot flushes, we base our sample size calculation on two separate clusters of information. From double-blind hot flush trials we can expect a moderate effect size of Cohen’s *d* = 0.40 given a mean of 19, standard deviations of 10 [23], and a four-point reduction in the hot flush score (frequency × severity) after 4 weeks of placebo [43]. Based on previous OLP trials in patients with irritable bowel syndrome and chronic low back pain, a large effect size of *d* = 0.80 can be expected [28, 30]. Combining these two clusters of information, a moderate to large effect size is expected for the difference between the OLP and the no-treatment groups at post-treatment. For a two-tailed Student’s *t*-test with an *α*-error rate of 0.05, a number of *N* = 90 participants would provide an 80% power to detect an effect of *d* = 0.60. We assumed an attrition rate of 10% and obtained our required sample size of *n* = 100 women.

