### Measures

#### Primary outcomes

The group difference between OLP and no-treatment in the hot flush composite score (frequency × severity) and bothersomeness of hot flushes at post-treatment are our primary outcomes. Women record number and severity of hot flushes in real-time, i.e., at occurrence, using a portable paper diary [25, 45]. Night sweats are recorded on subsequent mornings. The diary is the gold standard for assessing hot flushes [46] and has shown high reliability and validity [25]. In accordance with guideline recommendations, the severity of each hot flush is rated as mild, moderate, or severe [5]. The severity categories are predefined, which minimizes divergence due to subjective evaluations. In the day, mild hot flushes are *not* accompanied by sweating. Moderate hot flushes are accompanied by sweating, whereas severe hot flushes lead to disruption of current activity. At night, mild hot flushes are spotted by damp sheets/clothing, whereas moderate and severe hot flushes cause awakening. Severe hot flushes additionally necessitate actions like opening the window, removing sheets, etc. The Hot Flush Rating Scale [38] assesses bothersomeness, i.e., to what extent hot flushes are regarded as problematic and distressing and cause interference with daily life in the preceding week. The Hot Flush Rating Scale has good reliability and validity [38].

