#### Efficacy

For our primary outcome hot flush composite score, we conduct a linear mixed model for repeated measures using restricted maximum likelihood estimations with the intent-to-treat sample. We define group membership (OLP/no treatment), measurement point, and their interaction term as fixed effects. The baseline score is additionally included as a covariate. Measurement points are treated as repeated measures with an autoregressive residual covariance structure. Moreover, the model includes a random intercept to model between-subject differences. A normal distribution with an identity link is used. Since each data point reflects a weekly mean, up to five weekly means are included for each participant. Effect sizes are obtained by dividing the estimated group difference by the product of standard error by square root of the number of participants in the no-treatment group [68]. For our primary outcome bothersomeness of hot flushes, we will perform a linear mixed model with two data points at baseline and post-treatment. A post-hoc test comparing OLP with no-treatment will be conducted to test the group difference at post-treatment.

By fitting (generalized) linear mixed models, the analytical strategy for all secondary outcomes corresponds with the one described for the primary outcome. For metric outcomes (health-related quality of life and global improvement) we use a normal distribution with an identity link. For dichotomous outcomes (response), we use a binomial distribution with a logit link, and for count outcomes (hot flush frequency), we use a negative binomial distribution with a log-link.

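### Two primary outcomes of equal standing are each tested at 0.05 with no success rule; if either one counts as efficacy, the chance of a false rejection is about 7–10%, not 5%

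*Protocol article*

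**What the plan says.** The Abstract (Methods/design) lists the two outcomes together: "Primary outcomes are differences between the OLP and the no-treatment group in the hot flush composite score (frequency × severity), and bothersomeness of hot flushes". The Primary outcomes section repeats this: "hot flush composite score (frequency × severity) and bothersomeness of hot flushes at post-treatment are our primary outcomes". Neither place ranks one above the other.

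The Efficacy section analyses them separately and calls each a primary outcome: "For our primary outcome hot flush composite score, we conduct a linear mixed model for repeated measures", and later "For our primary outcome bothersomeness of hot flushes, we will perform a linear mixed model with two data points at baseline and post-treatment".

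The Statistical analyses section opens with the error rate: "All hypotheses are tested two-sided with an *α*-level of 0.05".

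The Power analysis section uses one of the two outcomes: "The power calculation is based on our primary outcome hot flush score". It spends the whole error rate on that outcome: "For a two-tailed Student’s *t*-test with an *α*-error rate of 0.05", 90 "participants would provide an 80% power to detect an effect of *d* = 0.60". With 10% attrition this becomes 100 women.

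Nowhere does the article order the two tests, divide the 0.05 between them, or state whether success on one or on both is needed to call OLP efficacious.

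**The concern.** The trial has one confirmatory question, whether OLP works for hot flushes, and two tests that can each answer it at the full 0.05. With two chances to succeed and no rule linking them, the error rate for the question as a whole is not fixed at the stated level.

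What is at stake is how a split result is read. If the score is significant and bothersomeness is not, or the reverse, the article gives no basis for calling the trial positive or negative. That choice would then be made with the results in view.

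**Working it through.** **The plan's own figure.** Inputs from Power analysis: d = 0.60, two-sided alpha 0.05, power 80%, attrition 10%. Allocation is 1:1 (Study design).

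- Normal approximation: n per arm = 2(1.960 + 0.842)² / 0.60² = 43.6, so 44.
- Exact noncentral t: 44.6, so 45 per arm, 90 in total, with power 80.4%.
- Attrition: 90 / 0.90 = 100.

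The sample size reproduces. It is correct for one outcome tested at the full 0.05.

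**Error rate if either outcome suffices.** Let Z1 and Z2 be the two test statistics, standard bivariate normal with correlation r when neither outcome is affected. The article gives no correlation, so r is an assumption and is shown over a range.

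- Any false rejection: 1 − P(|Z1| < 1.96 and |Z2| < 1.96). At r = 0 this is 1 − 0.95² = 9.75%.
- False rejection in favour of OLP only: 1 − P(Z1 < 1.96 and Z2 < 1.96). At r = 0 this is 1 − 0.975² = 4.94%.

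| Assumed r | Any false rejection (nominal 5%) | In favour of OLP (nominal 2.5%) |
|---|---|---|
| 0 | 9.75% | 4.94% |
| 0.3 | 9.51% | 4.76% |
| 0.5 | 9.07% | 4.54% |
| 0.7 | 8.35% | 4.17% |
| 0.8 | 7.81% | 3.90% |
| 0.9 | 7.04% | 3.52% |

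Either way of counting gives the same relative inflation: a factor of about 1.95 at r = 0 (9.75 / 5) and 1.4 at r = 0.9 (7.04 / 5).

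**What each possible rule would do, at 45 per arm and d = 0.60.**

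- *Fixed sequence, score first at 0.05:* family-wise error at most 5%; power for the score stays at 80.4%.
- *Both must be significant:* error at most 5%; joint power about 66% (r = 0) to 74% (r = 0.8) if d = 0.60 holds for both (normal approximation).
- *Bonferroni, 0.025 each:* family-wise error 4.9% at r = 0 and 4.0% at r = 0.8; power for the score falls to 71.4%. Restoring 80% needs 55 per arm, 110 analysed, and 110 / 0.90 = 122.2, so 123 enrolled.
- *Holm:* the score may have to pass 0.025, where its power is again 71.4%.

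**The case against.** The strongest reply is that the article contains no rule under which one success is enough. It joins the two outcomes with a plain conjunction, and if both had to be significant the error would not exceed 5%. Testing each hypothesis at 0.05 is also compatible with a fixed sequence, so the sentence on alpha is not wrong in itself and could stand unchanged under the remedy proposed here. The article is condensed, and a fuller protocol or a statistical analysis plan may hold the missing rule.

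Much of this stands. A reader might infer that the plan declares either outcome sufficient, and so runs at an inflated error rate as a matter of fact. The text does not support that; it leaves the rule open. But the point does not rest on silence alone. The article fixes 0.05 for every hypothesis, gives the two outcomes equal standing in three places, and sizes the trial at an undivided 0.05. An alpha split in another document would contradict that wording and reduce the stated power. An order or a both-must-succeed rule would fit, but neither is stated. Powering the trial on the score does not by itself rank the score first.

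Two further readings are tempting and should be resisted:

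- A reader might take 7–10% as the chance of falsely claiming that OLP works. That figure counts both tails; the corresponding chance in favour of OLP is 3.5–4.9% against 2.5%.
- A reader might regard bothersomeness as the only outcome exposed to reporting by women who know their allocation. The diary behind the composite score is also completed by those women (Blinding; Primary outcomes), and the Limitations section acknowledges subjective reporting bias in hot flush trials generally.

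**Conclusion.** The concern holds in conditional form. The article names two primary outcomes of equal standing, tests each at two-sided 0.05, powers one of them at the full 0.05, and states no rule that connects them. If a significant result on either is read as efficacy, the any-rejection rate is about 7–10% instead of 5%, or about 3.5–4.9% instead of 2.5% in favour of OLP.

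These figures assume no effect on either outcome, approximately normal test statistics, and a correlation between 0 and 0.9 that is not taken from the article. The sample size calculation is sound for the single test that it describes. An unconditional statement that the trial's error rate is inflated would go further than the text allows.

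**What to change.** By dated amendment, before the data are examined, specify a fixed sequence: test the hot flush composite score first at two-sided 0.05, and test bothersomeness at two-sided 0.05 only if the score is significant. State that a non-significant score makes any bothersomeness result descriptive. This order matches the outcome on which the trial was sized.

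The cost is wording and the amendment itself. The 90 analysed and 100 enrolled, and the 80% power for the score, are unchanged. The real downside is that bothersomeness loses its confirmatory claim if the score fails. Recruitment was under way when the article was written, and patients and clinicians know the allocation, so the amendment should record that the order was chosen without sight of outcome data.

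Holm also controls the error but is not free: at 0.025, power for the score at 45 per arm falls to about 71%. Requiring both outcomes is valid too, at a joint power of about 66–74% under the assumptions shown. Whichever rule is chosen, it should be stated once and applied to the conclusion.

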#### Missing data

To analyze diary data, we aggregate daily data so that each data point comprises a weekly mean (Fig. 2). Means are calculated if at least 3 days of the week are completed. Almost identical means of the hot flush diary were found for 3 and 7 days [66]. Missing data points are not replaced since, in linear mixed models, missing outcome data are handled using maximum likelihood estimation, assuming that data are missing at random conditional on information in the model. Single missing values in questionnaires are substituted by the mean of the remaining items, provided that 80% are completed [67].

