## Methods/design

### Study design

In this randomized-controlled, assessor-blinded superiority trial, menopausal women with hot flushes are assigned 1:1 to a 4-week OLP treatment or a no-treatment control group. The control group allows for examining whether OLP has beneficial effects over and above spontaneous improvement and statistical phenomena. Patients receive three study visits at enrolment, baseline, and post-treatment (Fig. 1). Women allocated to OLP are randomized a second time at post-treatment to either another 4 weeks of placebo (OLP 8wk) or to discontinue the treatment (OLP 4wk). Accordingly, OLP 8wk and OLP 4wk receive a fourth study visit at 8 weeks follow-up, whereas, for the no-treatment group, the study ends at week 4. Two calls at weeks 2 and 6 are conducted to inquire about adverse events and adherence. To further understand the experiences of participants and potential psychological mechanisms from their perspective, qualitative interviews will be conducted with a subgroup of patients who have reported improvements under the placebo. Ethics approval is given by the Physicians’ Chamber of Hamburg (reference number PV5787). The trial is registered at ClinicalTrials.gov (ID NCT03838523) and complies with the SPIRIT guidelines [37].

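### The rule against replacing missing diary weeks covers outcomes only, so a woman without a usable baseline week drops out of the composite-score model that is labelled intent-to-treat

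*Protocol article*

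**What the plan says.** Three statements in the protocol article bear on this point.

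- **Missing data, usable week.** Daily diary entries are averaged by week. "Means are calculated if at least 3 days of the week are completed"; otherwise that week has no value.
- **Missing data, no replacement.** "Missing data points are not replaced since, in linear mixed models, missing outcome data are handled using maximum likelihood estimation". The stated assumption is missingness at random given what is in the model.
- **Efficacy.** The composite-score model is fitted "using restricted maximum likelihood estimations with the intent-to-treat sample", with group, measurement point and their interaction as fixed effects. "The baseline score is additionally included as a covariate". Up to five weekly means per woman enter the model. Over a 4-week treatment this implies the baseline week plus weeks 1 to 4.

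Secondary outcomes follow the same strategy, so diary-based hot flush frequency is treated alike. For bothersomeness, the Efficacy section describes a model with two data points and does not repeat the covariate.

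**The concern.** The no-replacement rule is worded for all weekly data points, but its justification reaches only those that serve as outcomes. The baseline weekly mean also serves as a predictor. A mixed model conditions on its predictors, so a row with a missing predictor cannot contribute to the likelihood. Because the baseline value is the same on every row of a given woman, its absence removes all of them.

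Two things are at stake. Randomised women with observed post-treatment diaries could leave a primary analysis, with some loss of precision. The result would also be reported as intent-to-treat when the set is in fact restricted to women with a usable baseline week.

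**Working it through.** **1. Does anything in the protocol prevent the loss?**

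- Study sample and SV 1: eligibility and the enrolment interview ask about hot flushes. No completed diary week is required.
- SV 2: allocation is by opening the envelope. No diary check is described.
- Sensitivity analyses: last observation carried forward has no earlier value to carry into the baseline week.

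**2. Which rows enter the model?** Take a made-up data set of 100 women with five weekly means each (500 rows), where 5 women have no baseline value.

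| Model | Women kept | Rows kept |
|---|---|---|
| Group × week, baseline covariate | 95 | 95 × 5 = 475 |
| Group × week, no covariate | 100 | 500 − 5 = 495 |

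The first model discards 5 × 4 = 20 observed post-baseline means. Carrying the last observation forward left all 5 baselines empty.

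**3. The plan's own sample size.** Inputs from Statistical analyses, Study design and Power analysis: two-sided α = 0.05, 1:1 allocation, d = 0.60, N = 90, 10% attrition. With noncentrality d·√(n₁n₂/N) = 0.60 × √22.5 = 2.846 and 88 degrees of freedom, power is 80.4%. Also, 90/0.9 = 100. Both stated figures reproduce.

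**4. Cost of dropping the women.** The rate of unusable baseline weeks is not given, so 3, 5 and 10% of the 90 are assumed, leaving 87, 86 and 81 women. The correlation ρ between baseline and outcome is also not given; 0.5 and 0.7 are assumed. A single post-treatment time point with baseline adjustment (ANCOVA) is used as an approximation.

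- Women dropped: the effect becomes 0.60/√(1 − ρ²), on the reduced N, with N − 3 degrees of freedom.
- Baseline filled with the pooled mean: the effect becomes 0.60/√(1 − fρ²), where f is the share of observed baselines, on all 90 women, with 87 degrees of freedom.

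Example, ρ = 0.5 and 10% missing:

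- Dropped: 0.60/√0.75 = 0.693; × √(40 × 41/81) = 3.12; power 86.8%.
- Filled: 0.60/√(1 − 0.9 × 0.25) = 0.682; × √22.5 = 3.23; power 89.2%.

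| ρ | Missing | Dropped | Filled | Gain (points) |
|---|---|---|---|---|
| 0.5 | 3% | 89.1% | 89.8% | 0.7 |
| 0.5 | 5% | 88.8% | 89.7% | 0.9 |
| 0.5 | 10% | 86.8% | 89.2% | 2.4 |
| 0.7 | 3% | 97.2% | 97.3% | 0.0 |
| 0.7 | 5% | 97.1% | 97.1% | 0.1 |
| 0.7 | 10% | 96.2% | 96.4% | 0.3 |

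At a weaker ρ = 0.3 and 10% missing, the same formulas give 79.8% against 83.5%. Simulation of the same ANCOVA agreed with these gains to within about 0.3 points. With no true effect, the rejection rate with pooled-mean filling stayed near 5%.

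**The case against.** The strongest reply is that the Missing data section is correct as worded: it speaks of missing outcome data and claims nothing about covariates. On that view all that is left is silence about a missing baseline covariate, which a full protocol or analysis plan would normally settle. This stands in part, since the sentence on likelihood is true in itself. But the article does not leave the matter open. It rules out replacing data points in general, puts one of those points into the model as a covariate, and names the analysis set. Taken together, these statements yield a different set from the one named.

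A second reply is that unusable baseline weeks should be rare. An assessor explains the diary, completion is reimbursed, and only 3 days of the week are needed. That is fair; nothing in the protocol points to a high rate.

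A reader might also infer more than the protocol supports:

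- **Power falls clearly below 80%.** The unadjusted t-test gives 80.4% at N = 90 and 75.5% at N = 80. But the loss arises only because the model adjusts for baseline, and adjusted power at N = 81 is still about 87% at ρ = 0.5.
- **The treatment comparison is biased.** Baseline precedes allocation, so the arm cannot have caused the missing value. No between-arm bias is shown.
- **The 10% attrition allowance excludes this loss.** Power analysis does not define attrition, so this cannot be said either way.

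**Conclusion.** The point holds for the composite score and for diary outcomes modelled the same way, such as hot flush frequency. It should not be extended to bothersomeness. As written, the no-replacement rule and the baseline covariate together allow randomised women with observed weeks 1 to 4 to be left out of an analysis called intent-to-treat, and no other section prevents it.

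The size is modest: about 0 to 2 power points at d = 0.60. This rests on an assumed 3 to 10% of unusable baseline weeks, correlations of 0.5 to 0.7, and a one-time-point approximation to the repeated-measures model. The gain from retaining the women would be somewhat larger at a weaker correlation and nil if every baseline week is usable. The case for acting is mainly that the analysis set should match its label and that the repair is nearly free.

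**What to change.** State that the no-replacement rule applies to outcomes only. Where the baseline covariate is missing, fill it with the mean of all observed baselines, pooled over both arms and computed blind to outcome. Only the covariate is filled; the missing baseline week stays missing where it serves as an outcome row. Every randomised woman with at least one post-baseline weekly mean then stays in the model.

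Alternatively, drop the covariate and model baseline only as an outcome, with a common mean in both arms. This also keeps these women, but it is a different model rather than an equivalent one, so the choice should be fixed in advance.

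The cost of the first option is one sentence in the analysis plan. Neither option needs new data.

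Response, defined as change from baseline frequency, remains undefined without a baseline week and is not repaired by filling the covariate.

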**Fig. 2 Fig2:**
[figure not shown]
Study design with hypothesized trends of hot flush score. *SV* study visit, *OLP* open-label placebo, *wk* week. The *arrows* represent the point in time of the first and second allocation. *Circles* represent placebo intake, *squares* represent no placebo intake. OLP 4wk and OLP 8wk are subgroups of the OLP group

#### Efficacy

For our primary outcome hot flush composite score, we conduct a linear mixed model for repeated measures using restricted maximum likelihood estimations with the intent-to-treat sample. We define group membership (OLP/no treatment), measurement point, and their interaction term as fixed effects. The baseline score is additionally included as a covariate. Measurement points are treated as repeated measures with an autoregressive residual covariance structure. Moreover, the model includes a random intercept to model between-subject differences. A normal distribution with an identity link is used. Since each data point reflects a weekly mean, up to five weekly means are included for each participant. Effect sizes are obtained by dividing the estimated group difference by the product of standard error by square root of the number of participants in the no-treatment group [68]. For our primary outcome bothersomeness of hot flushes, we will perform a linear mixed model with two data points at baseline and post-treatment. A post-hoc test comparing OLP with no-treatment will be conducted to test the group difference at post-treatment.

By fitting (generalized) linear mixed models, the analytical strategy for all secondary outcomes corresponds with the one described for the primary outcome. For metric outcomes (health-related quality of life and global improvement) we use a normal distribution with an identity link. For dichotomous outcomes (response), we use a binomial distribution with a logit link, and for count outcomes (hot flush frequency), we use a negative binomial distribution with a log-link.

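### In the hot flush score model the baseline week appears to be both an outcome and a covariate, which makes the week-4 standard error too small

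*Protocol article*

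**What the plan says.** All references are to the Protocol article.

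- **Hot flush composite score (Efficacy).** A REML mixed model has group, measurement point and their interaction as fixed effects, a random intercept and autoregressive residuals. The text then states: "The baseline score is additionally included as a covariate". Because each data point is a weekly mean, "up to five weekly means are included for each participant".
- **Bothersomeness (Efficacy).** Here "we will perform a linear mixed model with two data points at baseline and post-treatment", followed by a test of the group difference at post-treatment. No baseline covariate is mentioned for this model.
- **Primary contrast (Primary outcomes).** For both outcomes it is the difference between open-label placebo and no treatment at post-treatment, that is, week 4.
- **Effect size (Efficacy).** The estimated group difference is divided by its standard error times the square root of the number of women in the no-treatment group.

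**The concern.** If the baseline week is one of the five outcome rows, using it as a covariate as well means that one row in five is regressed on itself. Its residual is artificially small. That lowers the variance pooled over all weeks and pulls the single baseline slope towards 1, away from the slope that suits week 4. The reported standard error of the week-4 difference is then smaller than the true one.

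What is at stake is the p-value and confidence interval for a declared primary outcome, and the standardised effect size built from the same standard error.

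**Working it through.** **Inputs from the Protocol article.** Allocation 1:1 (Study design); two-sided alpha 0.05 (Statistical analyses); "standard deviations of 10", and N = 90 analysed, so 45 per arm (Power analysis).

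**Assumptions.** No correlation between weekly scores is given. I take covariance 100 × [s + (1 − s)ρ^lag], with random-intercept share s from 0 to 0.8 and autoregression ρ from 0 to 0.8, equal variances over weeks, complete data and no treatment effect.

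**The plan's own figure.** For d = 0.60 and 45 per arm, the noncentrality is 0.60 × √(45/2) = 2.85 on 88 df, and exact power is 0.804. This reproduces N = 90, and 90/0.90 = 100. The sample size is not affected by this point. The plan gives no error rate for the mixed model.

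**Which week is the fifth?** Treatment before the primary comparison lasts four weeks, which gives four weekly means. Allocation follows enrolment by about a week (SV 1), which leaves a pre-allocation diary week as the fifth. Two other places treat baseline as a time level: the bothersomeness model and the Maintenance contrasts.

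**One setting in full (s = 0.5, ρ = 0.3).**
- Correlation of baseline with week 4: c = 0.5 + 0.5 × 0.3⁴ = 0.504.
- Common slope fitted by the model as written: b = 0.667. With weeks 1-4 only it is 0.558, and week-4 ANCOVA would use 0.504.
- True variance per woman: 100 × (1 + b² − 2bc) = 77.2. True SE of the difference: √(2 × 77.2/45) = 1.85.
- The model reports 0.864 of this, about 1.60.
- Type I error: 2[1 − Φ(1.96 × 0.864)] = 9.0%.

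**Range.** Week-4 type I error for the model as written, and for the same model with baseline removed from the outcome rows and nothing else changed. Simulations use 45 per arm and 2000 runs, so the Monte Carlo standard error is about 0.5-0.8 points.

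| s / ρ | SE ratio as written | As written, large-sample | Weeks 1-4 only, large-sample | As written, simulated | Weeks 1-4 only, simulated |
|---|---|---|---|---|---|
| 0 / 0 | 0.96 | 6.0% | 5.0% | – | – |
| 0.5 / 0 | 0.92 | 7.3% | 5.0% | 6.3% | 4.6% |
| 0.5 / 0.3 | 0.86 | 9.0% | 6.0% | 9.2% | 5.6% |
| 0.7 / 0.3 | 0.85 | 9.6% | 6.2% | 9.6% | 5.7% |
| 0.5 / 0.6 | 0.80 | 11.8% | 8.0% | 11.7% | 7.7% |
| 0 / 0.8 | 0.77 | 13.1% | 9.1% | 13.5% | 9.2% |
| 0.8 / 0.8 | 0.74 | 14.6% | 10.3% | – | – |

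The large-sample gap between the two models runs from 6.0 − 5.0 = 1.0 point to about 4.5 points. That gap is the part due to the double use.

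**Where the rest comes from.** Take s = 0.5 and ρ = 0.6. Baseline correlates 0.5 + 0.5 × 0.6 = 0.80 with week 1 but 0.5 + 0.5 × 0.6⁴ = 0.565 with week 4. The variance left after baseline is 1 − 0.80² = 0.36 at week 1 and 1 − 0.565² = 0.68 at week 4. One slope and one residual variance for all weeks average over this and understate week 4.

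**Cross-checks.** A separate REML simulation (five settings, 1000 runs each) gave 7.4-10.7% as written, against 3.9-4.8% for week-4 ANCOVA on the same data. A random-intercept-only fit (s = 0.5, ρ = 0.3, 828 runs) gave 7.0% as written and 5.2% with weeks 1-4 only. With a baseline SD 0.7 or 1.3 times the later SD, the model as written gave 7.5-12.1%.

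**Effect size.** SE ratios of 0.96 to 0.74 multiply it by 1/0.96 = 1.04 to 1/0.74 = 1.35. Both sources of error are included in this.

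**Bothersomeness, with r the baseline-to-post correlation.**
- As written, without the covariate: variance relative to ANCOVA is 1/(1 − r²), which is 1/0.75 = 1.33 at r = 0.5 and 1/0.51 = 1.96 at r = 0.7.
- If the covariate were carried over: b = (1 + r)/2, true variance 1 − 2br + b², and model variance the average of (1 − b)² and the true variance. At r = 0.5, b = 0.75, the true variance is 0.8125 and the model variance is (0.0625 + 0.8125)/2 = 0.4375. The SE ratio is √(0.4375/0.8125) = 0.734 and the type I error 15.0%. At r = 0.7 it is 15.7%.

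**The case against.** **The double use is inferred.** The sentence on five weekly means could describe everything the model uses, with baseline as covariate and weeks 1-4 as outcomes. Fig. 2, which would show the layout, is not available. This stands as a caveat. The five-row reading is still the more natural one, and under the other reading the single slope and covariance structure still give 5.0-10.3% in large samples.

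**Other tests from the same model behave better.** The joint group-by-time test rejects in 4.9-6.6% of simulations. The change-from-baseline contrast can be conservative (down to about 3%) but can also exceed 5%. This is true, but the plan's primary comparison is the difference at post-treatment, which is the affected test.

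**A reader might infer more than the text supports:**
- *That the whole excess comes from the double use.* It does not. Removing baseline from the outcomes alone leaves much of the excess when serial correlation is strong.
- *That both primary outcomes are tested invalidly.* The covariate is stated only for the composite score. The two-point bothersomeness model as written gives a valid, unadjusted comparison, in line with the t-test behind the sample size. The 15% applies only if the covariate is carried over. Nor does the text say that both the random intercept and the autoregressive residual apply there, so a claim that they cannot be separated has no firm basis.
- *That every secondary outcome inherits the fault.* Global improvement is itself a change rating and response is defined by change, so neither has a baseline value to use twice. For hot flush frequency, which has its own negative binomial model, no size was computed.

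**Conclusion.** The composite score model is wrong as written on its natural reading. In every setting tried, the week-4 standard error is too small, at 0.74-0.96 of its true value, and the type I error is about 6-15% instead of 5%. The double use accounts for about 1-4.5 points. The rest belongs to the single baseline slope and the constant-variance autoregressive structure. The standardised effect size is overstated by about 4-35% relative to the same formula with a correct standard error.

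The direction is secure if baseline is an outcome row. The size depends on correlations the documents do not give, so no single inflated rate should be quoted as the trial's. For bothersomeness the finding is lost precision and an unstated choice, not an invalid test. Because a primary p-value is affected, the wording should be corrected before data lock.

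**What to change.** **Composite score.** Use weeks 1-4 as the outcome rows. Fit group, week, group by week, baseline and baseline by week, with an unstructured covariance in place of the random intercept and autoregressive residual. Name the week-4 group contrast as the primary test. With complete data this reproduces week-4 ANCOVA, so it removes both sources of error; taking baseline out of the outcomes alone would remove only one. An alternative is to keep all five means, drop the covariate and constrain the two arms to a common baseline mean.

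**Bothersomeness.** Use ANCOVA of the post-treatment score on group and baseline, and say so explicitly.

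**Effect size.** Compute it from the corrected model.

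**Cost.** Only plan wording changes, with no new data or participants. The unstructured matrix for four weeks has 4 × 5/2 = 10 parameters, against 3 for a random-intercept variance, a residual variance and an autoregressive correlation. Baseline by week adds 3 slopes. That is a small price with about 90 women.
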